**Fourth Military Medical University**

**2011.06**

**Abstract**

**Background**: Periodontitis, which progressively destroys tooth-supporting structures, is one of the most widespread infectious diseases and the leading cause of tooth loss in adults. Evidence from animal studies indicates that stem cells derived from either bone marrow or the periodontal ligament (PDL) can be used in therapies for the regeneration of lost or damaged periodontal tissues. The aim of this clinical trial is to identify the safety of the clinical use of stem cells in periodontal therapy and to verify whether stem cells in combination with Bio-oss® are more effective than Bio-oss® alone in guided tissue regeneration (GTR) techniques for treating periodontal disease in human patients.

**Methods/Design**: In this protocol, we designed a single-center randomized trial to treat periodontal disease using GTR techniques and bovine-derived bone mineral (BDBM, Bio-oss®) with or without the incorporation of autologous periodontal ligament stem cells (PDLSCs). In total, approximately 30 periodontitis patients aged 18 to 65 years with a total of approximately 40 test teeth with periodontal intrabony defects and who satisfy our selection and exclusion criteria will be enrolled. These patients will be randomly assigned to either the Cell testing group (treatment with GTR and PDLSC sheets in combination with Bio-oss®) or the Control group (treatment with GTR and Bio-oss® without containing cells). During a 12-month follow-up, we will examine the extent of any adverse events related to the use of PDL cells. Moreover, the primary outcome is the magnitude of change in the alveolar bone height, and the secondary outcome measures are improvements in clinical attachment level (CAL), probing depth (PD), and gingival recession (GR).

**Discussion**: The results of this trial will assess the efficacy, safety and feasibility of using autologous PDLSCs to treat periodontal intrabony defects, and these data will provide primary clinical evidence for the future use of autologous stem cells in regenerative periodontal therapy.

**Background**

Periodontitis is an inflammatory disease that causes pathological alterations in tooth-supporting tissues and can lead to tooth loss if left untreated. National surveys have shown that the majority of adults suffer from moderate periodontitis, and up to 15% of the population is affected by severe generalized periodontitis at some stage of their lives [1,2]. The significant burden of periodontal disease and its impact on the general health and quality of life of the patient indicates a clinical need for the effective management of this condition [3]. Notably, the ultimate goal of periodontal therapy is the predictable regeneration of the functional attachment apparatus destroyed by periodontitis, which involves at least three unique tissues, *e.g.,* cementum, the periodontal ligament (PDL), and alveolar bone. To date, several regenerative procedures have attempted to achieve this ambitious goal, including guided tissue regeneration (GTR), bone graft placement, and the use of bioactive agents, such as growth factors (reviewed in [4-8]). However, current therapeutic techniques that are used either alone or in combination are limited in their ability to attain complete and predicable regeneration, especially in advanced periodontal defects. In these cases, remaining deep intraosseous defects following periodontal therapy have been shown to be high-risk sites for the further progression of periodontitis (reviewed in [9-12]).

According to the histological evidence, the GTR technique in combination with grafting materials, such as Bio-oss® (Geistlich Pharma AG, Volhusen, Switzerland) and autologous bone, is partially effective at treating periodontal defects; however, the currently available GTR-based therapies are rudimentary and show poor clinical predictability [4,5,8]. Recent advances in stem cell biology and regenerative medicine have enabled the use of cell-based therapies in periodontal diseases [8,16]. To date, a large number of animal studies have indicated that *ex vivo*-manipulated stem cells derived from either bone marrow or the periodontal ligament (PDL) can be used in conjunction with different physical matrices to regenerate periodontal tissues *in vivo* (reviewed in [7,8,13-19]).

**Methods/Design**

**Overview**

***Purpose***

The purpose of this clinical trial is to confirm the safety of autologous stem cells in clinical periodontal regenerative surgery and clarify the efficiency of autologous periodontal ligament (PDL) stem cells to form cell sheets that can be used to regenerate periodontal tissue in periodontitis patients with deep intraosseous defects (>5 mm). This study is a single-center, randomized, controlled study (Figure 1) that was approved by the ethical committees of School of Stomatology, Fourth Military Medical University (2011-02) and registered in the ClinicalTrials.gov database (reference no. NCT01357785). The study will be conducted according to the Declaration of Helsinki, and we will obtain consent from all enrolled subjects with regards to participation in this trial and contribution of trial data for non-commercial purposes. The protocol of this trial was externally reviewed and approved by an anonymous independent ethical review committee to ensure no serious ethical concerns. This study is a randomized clinical trial that includes a test and control group for comparison and involves only one dental facility (Translational Research Team, School of Stomatology, Fourth Military Medical University). The clinical trial will be conducted according to the schedule shown in Figure 1.

***Main outcome measures***

In this study, we will examine the extent of adverse events related to the use of PDL cells. In addition to the safety assessment, the main outcome measure in the study protocol is the magnitude of change in the alveolar bone height (primary outcome for efficacy).

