***Study Products***

Bio-Oss® and Bio-Guide® (Geistlich Pharma AG, Volhusen, Switzerland) and PDL cell sheets (cells obtained from a patient’s tooth/teeth; see inclusion criteria) will be produced at the Research and Development Center for Tissue Engineering (Fourth Military Medical University, [name]) using a standardized procedure (see section 5.1. cell products). Both transplants (Bio-oss® only or Bio-oss®/cell sheets) will be prepared (ready for immediate use) by the laboratory researchers, and Investigator 3, who will perform the follow-up study, will remain blinded to the treatment conditions.

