**Adverse events**

***Definition***

An adverse event is any unfavorable and unintended sign (including an abnormal laboratory finding), symptom, or disease that is temporally associated with the use of the investigational cells whether or not it is considered to be related to the investigational cells. We will examine the extent of any adverse events.

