***Evaluation of adverse events***

The investigators will record any adverse event with the exact name, onset date, severity, provided treatment and date of disappearance.

Each adverse event will be graded for severity using the following scale and criteria as outlined by the Ministry of Health and Welfare of the Chinese Government.

- **Mild**: The subject can continue the subsequent schedule without any treatment.
- **Moderate**: The subject can continue the subsequent schedule with treatment.
- **Severe**: The subject cannot continue the subsequent schedule.

The investigators will determine the relationship of the adverse event and the investigational cells.

The investigators will determine whether or not the adverse event is classified as a serious adverse event. A serious adverse event is defined as any experience suggesting a significant hazard, contraindication, side effect, or precaution. A serious adverse event includes any adverse experience resulting in any of the following outcomes:

- Death
- A life-threatening adverse experience
- Impatient hospitalization or prolongation of existing hospitalization
- A disability/incapacity that may interfere with the subject's daily life
- An adverse experience leading to a disability/incapacity
- A serious adverse experience at the same level as the above conditions
- A congenital anomaly/birth

**Efficacy assessment** [34,35]

The main outcome measure in the study protocol is change in the alveolar bone height at 3, 6, and 12 months post-operation. We set the rate of increase in alveolar bone height as the most statistically important outcome (primary outcome). The clinical attachment level (CAL), probing depth (PD), and gingival recession (GR) are generally used to assess pathology in periodontal disease. These parameters do not directly assess the efficacy of cells in periodontal tissue regeneration and were selected in the present study as secondary outcome measures to ascertain whether cells would cause abnormal periodontal healing following periodontal surgery. These measurements will be recorded at baseline and 12-months post-surgery.

***Standardized radiography and dental CT for regions of investigation*** [34,35]

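### The main safety outcome is worded in two conflicting ways: adverse events related to the cells in one place, all adverse events whatever their relation in another

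*Protocol*

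**What the plan says.** Safety is the first aim in the Abstract and under Purpose. The protocol then describes what will be examined in two ways.

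- **Restricted.** Main outcome measures: "we will examine the extent of adverse events related to the use of PDL cells". Abstract: "we will examine the extent of any adverse events related to the use of PDL cells".
- **Unrestricted.** Adverse events, Definition: an event is one "temporally associated with the use of the investigational cells whether or not it is considered to be related to the investigational cells". The same section closes with "We will examine the extent of any adverse events".

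Evaluation of adverse events keeps recording and attribution apart. On recording: "The investigators will record any adverse event with the exact name, onset date, severity, provided treatment and date of disappearance". On attribution: "The investigators will determine the relationship of the adverse event and the investigational cells". Study Design gives follow-up and safety assessment to Investigator 3, and Study Products says that "Investigator 3, who will perform the follow-up study, will remain blinded to the treatment conditions".

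**The concern.** The restricted wording stands in the outcome section and the Abstract, where a reader looks for the outcome. Applied literally, it drops a recorded event from the main safety outcome once that event is put down to something other than the cells. Every cell-treated tooth also undergoes surgery and receives Bio-oss®, so a local event can have a plausible alternative cause.

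For a new cell product, whether an event is related to the cells is something the trial should learn from the data. If relatedness is a condition for being counted, the outcome reflects the judgement as well as the harm. With two wordings available, the choice between them could also be left until the results are known.

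**Working it through.** **Comparison of the text**

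| Place in the protocol | Which events | Role of judged relation |
|---|---|---|
| Abstract; Main outcome measures | those related to use of the cells | part of the outcome wording |
| Adverse events, Definition | any, in temporal association with use of the cells | expressly irrelevant |
| Evaluation of adverse events | any event is recorded | determined separately by the investigators |

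Two things follow.

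1. The first two rows conflict. The third supplies the judgement that would be needed to apply the first.
2. Events judged related are a subset of all events. Moving from the second row to the first can leave the count unchanged or lower it, and can never raise it.

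The Definition has a gap of its own. It ties an event in time to use of the cells, so read literally it gives no definition for a patient who receives only the control treatment.

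**Illustration of size**

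The protocol states no adverse event rate, so there is no figure of its own to reproduce.

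Inputs from the protocol: about 30 patients and about 40 teeth (Patients and enrolment); at most 2 teeth per patient, one to each group when there are two, and an even chance of either group when there is one (Study Design). Taking 30 and 40 as exact:

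- two-tooth patients: 40 − 30 = 10
- one-tooth patients: 30 − 10 = 20
- patients expected to receive cells: 10 + 20/2 = 20
- patients expected to receive control only: 20/2 = 10

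Assumptions that are not in the protocol: a per-patient event risk p, a share f of events judged related, and independent patients with at most one event each.

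Expected patients counted = 20 × p × f. Chance that none is counted = (1 − p × f)^20.

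| p | All events (f = 1) | f = 0.75 | f = 0.50 | f = 0.25 |
|---|---|---|---|---|
| 10% | 0.12 | 0.21 | 0.36 | 0.60 |
| 20% | 0.012 | 0.039 | 0.12 | 0.36 |
| 30% | 0.0008 | 0.006 | 0.039 | 0.21 |

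For example, at p = 20% and f = 0.25 the expected count falls from 20 × 0.20 = 4 to 20 × 0.05 = 1. The chance of a zero count rises from 0.80^20 = 0.012 to 0.95^20 = 0.36.

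**The case against.** The strongest reply is that the outcome sentence is a loose overview and that the detailed section governs. Main outcome measures says neither that only related events count nor that relatedness is judged before counting. The Definition fixes the meaning of the term without regard to relation, and Evaluation of adverse events requires every event to be recorded. Read that way, nothing is lost. This reading is at least as natural as the literal one, and it is why the concern is a risk and not a fixed defect.

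A reader might go further and infer that the protocol removes events judged unrelated from its safety result. It does not say so: no section drops such events from counting, analysis or reporting. Nor do the documents support a claim that the two wordings would give opposite safety conclusions, because the protocol sets no safety threshold or hypothesis that could reverse.

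Blinding is also a fair point. If Investigator 3 judges relatedness while blinded, events at cell-treated sites cannot knowingly be discounted more than those at control sites. But the protocol assigns the judgement to the investigators in general, and blinding does not prevent under-counting in both groups alike.

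The lack of stated criteria for relatedness carries no weight here, since a statistical analysis plan or safety manual may supply them. The conflict in the outcome wording is different: it lies in the protocol itself, and a later document could only choose between the two wordings.

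**Conclusion.** The concern holds as an inconsistency in the main safety outcome of a trial whose first aim is safety. The literal reading of Main outcome measures puts a causality judgement between the recorded events and the headline result, and its effect on the count runs one way only. Whether any event would in fact be left out cannot be determined from the protocol.

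The direction needs no assumption. The size does: the probabilities above rest on assumed event risks of 10% to 30%, assumed related shares of 25% to 75%, and 20 cell-treated patients derived from approximate planned numbers. They show that the choice of wording can matter in a trial of this size; they do not predict what it will observe. The correction is worth making because it is specific and cheap, and the data needed are largely planned already.

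**What to change.** 1. In the Abstract and under Main outcome measures, state the safety outcome as all adverse events after study surgery, in both groups, irrespective of judged relation to the cells.
2. Keep the investigators' relatedness judgement, but report it only as a secondary description of those events.
3. In the Definition under Adverse events, anchor the time reference to study surgery instead of use of the cells, so that patients who receive only the control treatment are covered. Aligning the outcome wording with the present Definition would not achieve this.

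The cost is a few words in three places. Recording of any adverse event is already required, but because the present definition is tied to the cells, it should be confirmed that events are recorded in control-only patients on the same terms. The reported event rate may look less favourable, since events due to surgery or graft will be included; the comparison between groups and the secondary relatedness description put those events in context.

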**Study Design**

Each patient will be examined by at least five independent principal investigators. Investigator 1 will perform a basic oral examination using a clinical inspecting apparatus and X-ray, check all of the inclusion and exclusion criteria, and ensure that the informed consents are signed by the patients at the Registration Center. Next, Investigator 2 will perform the pre-surgical treatments, re-check the inclusion and exclusion criteria, and extract the tooth/teeth that will be subjected to cell isolation by Investigator 4. Investigator 2 will select no more than 2 teeth (from different regions) to be investigated in each patient. Following the collection of baseline data from the selected tooth/teeth by Investigator 3, Investigator 4 will culture the cells, make the cell products, and create an allocation table consisting of 2 cases per block that will be allocated to the Control group (Bio-oss® only) and Cell group (Bio-oss® and cell sheets). According to this allocation table, a label indicating the corresponding group will be attached to each tooth; thus, each tooth will be randomly assigned to one of the two treatment groups. The maximum number of teeth from one patient will be 2. Hence, if one tooth is allocated to the Control group, the other will be automatically assigned to the Cell group. However, if a patient only has one tooth chosen for investigation, it has a fair chance of being allocated to either group. Once a tooth is assigned to a group, it will be kept in a secure locked drawer inaccessible to all other study personnel. All of the patients will receive oral hygiene instructions, a tooth cleaning and basic dental therapies if needed, such as cavity filling and occlusal adjustment. The periodontal surgery will be performed 4-5 weeks after these pre-surgical treatments. When the oral condition and cell products are both ready for surgery, Investigator 4 will be asked to give the assigned implants (Bio-oss® only or a combination of Bio-oss® and cell sheets) to the physician (Investigator 5), who will then perform the surgery. This procedure ensures that the randomization is not influenced by the physicians taking part in this study. Investigator 4 will record the patients’ details and number the envelope assigned to each tooth. Investigator 3 will perform the follow-up study (data collection, safety assessment, etc.) of the patient, and the blind will not be broken until this clinical trial is completed.

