We expect to complete patient recruitment by December 2014 and anticipate that the results of this study will have implications for oral health care and facilitate improvements in the treatment of people with periodontitis. The results of this study will also allow us to determine if cell-based intervention is safe and effective for human dental use in clinical trials. These results may have important implications for the design of subsequent clinical trials and the development of sustainable, cost-effective cell-products for people with periodontitis.

This study will use central randomization, which is a strict and complete randomization method that ensures adequate concealment. The surgeon and the investigator who collect baseline and follow-up data will work independently in this trial. Throughout the entire trial, the patients are not aware of their group assignment. They will be told only that they will receive a periodontal surgery treatment that potentially includes cell products. This trial is a single-center randomized controlled study of approximately 30 patients that includes a 12-month follow up. This trial will be the first randomized controlled trial to address the effectiveness of cell therapy in combination with GTR and bone replacement for periodontitis.

In conclusion, stem cell therapy is a promising nascent therapy that may lead to the regeneration of lost periodontal tissue. Regenerative dentistry is at the forefront of the transition of basic science research to the clinical reconstructive arena. Although there are many issues that need to be resolved before stem cell therapies become commonplace, clinicians should continue to monitor the progression of these technologies.

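### The protocol claims concealed central randomisation, but the investigator who makes the cells also creates, holds and releases a blocks-of-2 allocation table

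*Protocol*

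**What the plan says.** The Protocol's Study Design section sets out the sequence. Investigator 1 checks eligibility and consent. Investigator 2 rechecks eligibility and selects at most two teeth per patient. The next step opens "Following the collection of baseline data from the selected tooth/teeth by Investigator 3", and then "Investigator 4 will culture the cells, make the cell products, and create an allocation table consisting of 2 cases per block". Under this table "each tooth will be randomly assigned to one of the two treatment groups".

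Two rules follow. For two-tooth patients: "Hence, if one tooth is allocated to the Control group, the other will be automatically assigned to the Cell group". For the others: "if a patient only has one tooth chosen for investigation, it has a fair chance of being allocated to either group".

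Assignments go into a locked drawer closed to other study staff. Investigator 4 records the patients' details, numbers the envelope for each tooth and hands the assigned implant to the surgeon (Investigator 5). The section says this keeps the physicians from influencing the randomisation. It says nothing about the laboratory.

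The Discussion section describes the method differently: "This study will use central randomization, which is a strict and complete randomization method that ensures adequate concealment". The protocol names no central or independent body that generates or holds a list.

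**The concern.** The two descriptions cannot both be right. Central randomisation means that someone outside the treating and product-making team generates and holds the list. In Study Design one person inside the team does both. That person also learns who the patient is and, from culturing the cells, how the product is developing. No step is said to fix the table before the first patient, and the text places its creation after baseline data are in.

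Concealment protects the comparison of bone gain between arms only if the person controlling assignment cannot choose it. Here the safeguards face everyone except that person. In a trial of about 40 teeth, a few discretionary assignments could matter. A reader of the Discussion would also credit the trial with a protection that its procedure does not provide.

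A second, smaller problem is that the protocol does not say what a block of two cases is. It could be the two teeth of one patient or two consecutive teeth in the trial. It also does not say how a patient with a single tooth enters a block.

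**Working it through.** The protocol gives no figure on this point to reproduce. The check sets the sections side by side and counts what the stated procedure implies.

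**Who does what (Study Design)**
- Generates the table: Investigator 4.
- Holds it: a locked drawer closed to all others.
- Numbers envelopes, records patient details, releases the implant: Investigator 4.
- Central or independent party: none described.

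This does not match the Discussion's claim of central randomisation. Nor is it complete randomisation, in which each allocation is independent of the previous ones. In a block of 2 the second is the opposite of the first.

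**Numbers of patients.** Patients and enrolment plans about 30 patients and 40 teeth, and Study Design says "The maximum number of teeth from one patient will be 2". Let s be one-tooth and p two-tooth patients:
- s + p = 30 and s + 2p = 40, so p = 10 and s = 20.

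**Predictability with blocks of 2**
- One-tooth patients on their own list: every second allocation is fixed, so 20/2 = 10 of 20.
- One shared tooth-level table: a two-tooth patient uses two positions and does not change odd or even. The 2nd, 4th, 6th and so on one-tooth patients therefore close a block, again 10 of 20.
- Someone who knows the block size and the previous allocation guesses correctly with probability 0.5 × 0.5 + 0.5 × 1 = 0.75, against 0.50 under complete randomisation.

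**Does the table clash with the two-tooth rule?**
- Reading A, a block is one patient's two teeth: the two entries always differ, so there are 0 clashes.
- Reading B, one sequential tooth-level table for all, patients arriving in random order: a two-tooth patient straddles two blocks when an odd number of one-tooth patients came before. With 20 one-tooth patients that number is equally likely to be 0 to 20, and 10 of these 21 values are odd. Expected straddles = 10 × 10/21 = 4.76. The two entries then come from independent blocks and agree half the time, so expected clashes = 4.76/2 = 2.38. Simulating 30,000 recruitment orders gives 4.77 and 2.38.

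Because the planned size is approximate, Reading B was varied:

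| Patients / teeth | One-tooth, two-tooth | Straddles | Clashes (formula) | Clashes (simulated) |
|---|---|---|---|---|
| 30 / 40 | 20, 10 | 10 × 10/21 = 4.76 | 2.38 | 2.38 |
| 28 / 40 | 16, 12 | 12 × 8/17 = 5.65 | 2.82 | 2.83 |
| 32 / 40 | 24, 8 | 8 × 12/25 = 3.84 | 1.92 | 1.92 |
| 30 / 38 | 22, 8 | 8 × 11/23 = 3.83 | 1.91 | 1.91 |
| 30 / 42 | 18, 12 | 12 × 9/19 = 5.68 | 2.84 | 2.86 |

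Clashes thus run from 0 under Reading A to about 1.9-2.9 under Reading B.

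**The case against.** The protocol does separate roles. Investigator 4 is not said to enrol patients or choose teeth. Baseline data are collected by someone else before allocation. Assignments are locked away and envelopes numbered, and the follow-up investigator and the radiographic examiners are blinded. All of this stands. It limits measurement bias and influence by other staff, but it does not bind the person who makes and holds the list.

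Three stronger readings are tempting, and the document does not support them.

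- *The table cannot be followed.* A reader might infer a flat contradiction with the two-tooth rule, since under Reading B at least one clash occurs in 92% of simulated trials. But the rule opens with the word *Hence*, which presents it as following from the block and the two-tooth maximum. That fits Reading A, where nothing clashes. One-tooth patients are then treated separately. Figure 1, which is said to show the randomisation, is not available here. What remains is an ambiguity.
- *Better-growing sheets could be steered between arms.* Control teeth receive no cells, and each two-tooth patient contributes one tooth to each arm, so cell growth cannot favour one arm there. The residual discretion is over which arm a one-tooth patient enters, and over which tooth of a pair gets cells if the defects are known to differ. The protocol does not say that Investigator 4 sees the baseline measurements.
- *The surgeon can predict and exploit the next allocation.* The surgeon may recognise the implant, but has no stated role in enrolment or tooth selection. That is a question of blinding, not a demonstrated failure of concealment.

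**Conclusion.** The concern holds: the protocol is wrong as written on who randomises and on the property claimed for the method. Its Discussion asserts central, complete, concealed randomisation. Its Study Design section gives generation, custody and release to the investigator who makes the product, using permuted blocks of 2.

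The exposure is mainly in the roughly 20 one-tooth patients, where 10 of 20 allocations are fixed by the preceding one, and in the choice of which tooth gets cells in the roughly 10 two-tooth patients. These counts assume exactly 30 patients and 40 teeth, and blocks of 2 applied to one-tooth patients. The clash figures also assume Reading B and random arrival order, and should be quoted only with the alternative of 0. Nothing in the document shows that any allocation would in fact be steered. The point is that the stated procedure does not prevent it.

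**What to change.** Amend the randomisation paragraph in Study Design and bring it into line with the Discussion:

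1. Have the list generated before the first patient by someone outside the laboratory and clinic, and held in the central system that the Discussion promises. Name the holder by role.
2. For two-tooth patients, draw at random which tooth receives cells, with the teeth ordered by a fixed rule set in advance.
3. For one-tooth patients, keep a separate list with undisclosed block sizes that are not fixed at 2.
4. Release each allocation to Investigator 4 only after eligibility is confirmed, the teeth are selected and baseline is locked, at a time compatible with preparing the sheets.

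Separate lists remove the clash under either reading of the block.

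The cost is one amended paragraph, plus a central holder who must actually exist, since the protocol promises one without describing it. The statistical price is a possible imbalance of a few one-tooth patients: if the largest block were 6, for example, an unfinished last block could leave one arm at most 3 ahead.
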